### 2.1. Study Design

This study is a randomized, prospective, single-blind clinical trial with a three-group cross-over design. Due to the design of the study, complete blinding is not possible. Statistical analysts are blinded on the groups to be compared. The randomization procedure and allocation are done through a person who was not further involved. [name] are responsible for the test setup and finally carry out the tests.

Patients are only informed about the performance but not about the target character of the tests. After receiving written informed consent, three patients are randomly assigned to either group A, B, or C (Table 1) and therefore run the test battery with rigid orthosis, soft brace and without aids in a cross-over order.

The bioelectrical activity of the gluteus medius and semitendinosus muscles are recorded using sEMG according to Surface ElectroMyoGraphy for the Non-Invasive Assessment of Muscles (SENIAM) guidelines [25]. Surface electrodes are placed on the involved and uninvolved limbs.

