## Abstract

A randomized crossover trial was designed to investigate the influence of muscle activation and strength on functional stability/control of the knee joint, to determine whether bilateral imbalances still occur six months after successful anterior cruciate ligament reconstruction (ACLR), and to analyze whether the use of orthotic devices changes the activity onset of these muscles. Furthermore, conclusions on the feedforward and feedback mechanisms are highlighted. Therefore, twenty-eight patients will take part in a modified Back in Action (BIA) test battery at an average of six months after a primary unilateral ACLR, which used an autologous ipsilateral semitendinosus tendon graft. This includes double-leg and single-leg stability tests, double-leg and single-leg countermovement jumps, double-leg and single-leg drop jumps, a speedy jump test, and a quick feet test. During the tests, gluteus medius and semitendinosus muscle activity are analyzed using surface electromyography (sEMG). Motion analysis is conducted using Microsoft Azure DK and 3D force plates. The tests are performed while wearing knee rigid orthosis, soft brace, and with no aid, in random order. Additionally, the range of hip and knee motion and hip abductor muscle strength under isometric conditions are measured. Furthermore, patient-rated outcomes will be assessed.

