### 2.2. Participants

Participants will be recruited at the Sporthopaedicum, Center for Orthopaedics, Sports Medicine and Orthopaedic Surgery in Berlin (Germany) and the University Hospital of Brandenburg, Center for Orthopaedics and Traumatology (Germany). Suitable patients are selected via a file review and invited for a surveillance test. The test battery is performed six months (+/−1 month) postoperatively to observe the greatest possible difference while reducing the risk of reinjury to a minimum.

The studied cohort of 28 patients consists of female and male patients. Only a large impact on performance is internally valid for estimating whether braces or orthoses should be worn as they are used to reduce adverse events. For this reason, a potential cut off for wearing braces or orthoses was set at a large estimated effect. A large effect for the investigated three degrees of freedom, with an acceptable alpha error of 0.05 and a 1-beta error of 0.9, results in a required total sample size of 27 when using an ANOVA: fixed effects, special, main effects, and interactions model. To catch up one possible drop out, which is not expected, a sample size of 28 is included.

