### 2.3. Procedure

The examination is performed in a single session, including three runs of the modified BIA test battery.

The patients are asked to abstain from unaccustomed strenuous exercise for at least 24 h before the testing and avoid eating a heavy breakfast in the morning before the test and no rich meals within two hours of the test. They are advised to wear comfortable sports outfits and indoor sports shoes. Only the double-leg and single-leg stability tests are carried out barefoot.

SEMG electrodes are applied to all participants on the ACL-reconstructed and unaffected legs on gluteus medius and semitendinosus muscles to measure muscle activation throughout the whole test battery.

After block randomization to determine the group, participants complete the test battery as presented in Table 2. For fatigue reasons, the unaffected limb is only tested in the first run. The best performance from each trial is selected for analysis.

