## 4. Data Analysis and Planned Statistical Analysis

All data are presented in a descriptive manner, including anthropometric data and absolute measured values. Side-to-side differences are calculated for all SL tests, using the limb symmetry index (LSI). Therefore, absolute values of the ACL-reconstructed leg are divided by the values of the unaffected leg and multiplied by 100. For the stability, quick feet and speedy tests LSI is calculated by dividing the measured value of the unaffected leg by the value of the ACL-reconstructed leg and multiplied by 100 according to the calculation done in the study by Herbst et al. [17].

Power is quantified in the sagittal plane and defined through force and velocity. This parameter is directly extracted from the force plate data and reported as extracted. It is assessed for jumping during loading phase and total jump height. Power is based on peak power calculations for the lower extremity, which is defined in newton for maximal applied force during contraction. Additionally, it will be interpreted in the context of recent LSI-papers.

Descriptive quantitative data are calculated as the mean ± standard deviation. The Kolmogorov-Smirnov test is used to test the normality assumption. To compare the variances across the means of the three groups we use ANOVA repeated measures. Wilcoxon and Friedman-Test are used as well to calculate between-group differences.

All statistical analyses are performed using SPSS (IBM SPSS Statistics, New York, NY, USA). The significance level for all statistical tests is set a priori to 0.05. A post-hoc power analysis is conducted when significant effects are found.

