## Figures and Tables

**Table 1 healthcare-11-00513-t001:** Individual group test setup.

Run	Group A	Group B	Group C
1	orthosis	brace	no aid
2	brace	no aid	orthosis
3	no aid	orthosis	brace

**Table 2 healthcare-11-00513-t002:** Description of the planned consecutive activities during the measurement session [17,35].

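### Table 1 uses only three cyclic device orders, so carry-over from one device to the next is partly confounded with the device effect and costly to adjust for

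*Protocol article*

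**What the plan says.** Section 2.1 (Study Design) describes a three-group crossover in which "three patients are randomly assigned to either group A, B, or C (Table 1) and therefore run the test battery with rigid orthosis", then with the soft brace and without aids in crossover order. Table 1, titled "Individual group test setup", gives the orders:

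| Run | Group A | Group B | Group C |
|---|---|---|---|
| 1 | orthosis | brace | no aid |
| 2 | brace | no aid | orthosis |
| 3 | no aid | orthosis | brace |

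Section 2.3 (Procedure) adds: "The examination is performed in a single session, including three runs of the modified BIA test battery", and says that groups come from block randomisation. It also recognises that earlier runs can affect later ones: "For fatigue reasons, the unaffected limb is only tested in the first run". The Abstract describes the conditions as applied in random order, which here means one of three orders.

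For the analysis, Section 4 says: "To compare the variances across the means of the three groups we use ANOVA repeated measures". Friedman and Wilcoxon tests are named as well. No carry-over term is named.

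**The concern.** Hypothesis 1 is a three-way comparison of orthosis, brace and no aid. A crossover answers it cleanly only if what was worn in one run does not alter the next, or if the orders allow such an effect to be separated from the device effect. In Table 1, whenever a condition has a predecessor, brace follows orthosis, no aid follows brace, and orthosis follows no aid. The three reverse successions never occur.

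A residual effect of the orthosis would therefore appear as an effect of the brace. A residual effect of the brace would shift the no-aid reference. Device-specific carry-over is plausible here: the runs share one session, and the Introduction suggests that devices may act through skin contact and a feeling of safety. The choice of orders is a design feature. Once the data are collected, no analysis plan can supply successions that were never run.

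**Working it through.** **Inputs.** Orders from Table 1. N = 28 from Section 2.2, which is 10/9/9 over three orders (equal allocation assumed, since no ratio is stated). Within-patient variance is σ². L_O, L_B and L_N are the residual effects of orthosis, brace and no aid on the next run. Their sizes are assumptions; the article gives none. It also gives no figure of its own on this point to reproduce.

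**Step 1: successions.** Each group contributes two.

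| Succession | Table 1 | All six orders |
|---|---|---|
| orthosis → brace | 2 | 2 |
| brace → no aid | 2 | 2 |
| no aid → orthosis | 2 | 2 |
| brace → orthosis | 0 | 2 |
| no aid → brace | 0 | 2 |
| orthosis → no aid | 0 | 2 |

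Each condition occurs once in each run of Table 1, so run effects shared by all conditions cancel. Within runs 2 and 3, the current device determines the previous one. Device and carry-over indicators then coincide, and device contrasts cannot be estimated with carry-over in the model. Run 1 has no predecessor, so over all three runs the aliasing is partial.

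**Step 2: bias without a carry-over term.** With Table 1 (balanced), two of every three observations on a condition have a predecessor, always the same one. The condition means therefore gain:
- brace: (2/3) L_O
- no aid: (2/3) L_B
- orthosis: (2/3) L_N

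With six orders, each of the other two conditions is the predecessor in one third of observations:
- brace: (1/3)(L_O + L_N)
- no aid: (1/3)(L_O + L_B)
- orthosis: (1/3)(L_N + L_B)

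Set L_O = L and the others to 0:

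| Contrast | Table 1 | Six orders |
|---|---|---|
| brace − no aid | 0.67 L | 0 |
| brace − orthosis | 0.67 L | 0.33 L |
| orthosis − no aid | 0 | −0.33 L |

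At 28 patients the slight imbalance moves these a little. With 10/9/9 they are 0.68 L, 0.67 L and 0.01 L. With 5/5/5/5/4/4, depending on which two orders are short, they are within ±0.06 L, 0.30 to 0.37 L, and −0.30 to −0.37 L.

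**Step 3: precision.** The model is outcome = patient + run + device + carry-over (runs 2 and 3) + error, fitted by least squares within patients.

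Without carry-over, the variance of a device contrast is 2σ²/N = 2/28 = 0.0714 σ² (0.0715 at 10/9/9).

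With carry-over, for balanced orders, the information on device contrasts is N, that on carry-over contrasts is 2N/3 − N/9 = 5N/9, and the cross-term is cN in size, with c = 2/3 (Table 1) or 1/3 (six orders), as in Step 2. The device information left after adjustment is N − (cN)²/(5N/9) = N(1 − 9c²/5):
- Table 1: N(1 − 0.8) = N/5, so the variance is multiplied by 5 and the standard error by √5 = 2.24.
- Six orders: N(1 − 0.2) = 4N/5, so the variance is multiplied by 1.25 and the standard error by √1.25 = 1.12.

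At N = 28 this gives 5 × 0.0714 = 0.357 σ² and 1.25 × 0.0714 = 0.089 σ². Fitting the actual design matrices gives 0.353 to 0.368 σ² for 10/9/9 and 0.087 to 0.092 σ² for 5/5/5/5/4/4.

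**The case against.** A three-order Latin square is a legitimate crossover. It removes patient effects and common run effects, so general practice and fatigue are dealt with, and it divides evenly at the required 27 (9/9/9). It is as precise as six orders if carry-over is absent. All of this stands.

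The article does not show that carry-over exists. The Introduction's remarks on skin contact describe a device while it is worn, and improvement from repeated jumping is a run effect if common to all conditions. The authors' pilot study in healthy participants found no influence of either device on the test results, although that does not settle the question after reconstruction. A reader might infer that the protocol's own theory predicts carry-over; the text supports only that it is plausible.

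A reader might also infer that Table 1 makes carry-over impossible to check. The finite adjusted variance shows otherwise, and run 1 alone is a randomised comparison free of carry-over, though between patients.

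Finally, six orders are not better for every contrast. For an orthosis residual, orthosis versus no aid is unbiased under Table 1 but shifts by about −0.33 L without adjustment under six orders.

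The article's silence on the interval between runs is not counted here, since the full protocol may give it. None of these points removes the fivefold cost of adjustment, which is fixed by the chosen orders.

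**Conclusion.** The point holds in limited form. Table 1 balances run effects but not successions. Device-specific carry-over is completely aliased with device in runs 2 and 3 and partly over the whole session. Unadjusted, an assumed orthosis residual L biases two of the three device contrasts by about two thirds of L. With six orders the largest bias is halved but not removed. The stronger argument is precision: the carry-over-adjusted comparison keeps about 20% efficiency under Table 1 and about 80% under six orders. With 28 patients and a sample sized for a large effect, the adjusted result under Table 1 would be a weak check on Hypothesis 1.

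This rests on carry-over that lasts one run, a within-patient analysis, near-equal allocation and complete data. Whether L differs from zero cannot be judged from the article. The change should be made because it is cheap insurance; the present design has not been shown to give a wrong answer.

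**What to change.** Before enrolment, randomise to all six orders (a Williams design) in blocks of six. For 28 patients, four full blocks and four places of a fifth give 5/5/5/5/4/4. Add the three reverse orders to Table 1. Keep the planned device comparison, and add a sensitivity analysis with run and first-order carry-over terms, reported for all three device contrasts. The analysis is needed as well as the orders, because six orders alone leave up to about one third of L in the unadjusted contrasts.

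The cost is a new randomisation list, three more orders in Table 1, and sequence sizes that differ by one (already so at 10/9/9). No patients, tests or session time are added, and essentially no precision is lost if carry-over is absent. Section 2 says ethical approval is still under consideration, so the change is realistic at this stage.

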### 2.2. Participants

Participants will be recruited at the Sporthopaedicum, Center for Orthopaedics, Sports Medicine and Orthopaedic Surgery in Berlin (Germany) and the University Hospital of Brandenburg, Center for Orthopaedics and Traumatology (Germany). Suitable patients are selected via a file review and invited for a surveillance test. The test battery is performed six months (+/−1 month) postoperatively to observe the greatest possible difference while reducing the risk of reinjury to a minimum.

The studied cohort of 28 patients consists of female and male patients. Only a large impact on performance is internally valid for estimating whether braces or orthoses should be worn as they are used to reduce adverse events. For this reason, a potential cut off for wearing braces or orthoses was set at a large estimated effect. A large effect for the investigated three degrees of freedom, with an acceptable alpha error of 0.05 and a 1-beta error of 0.9, results in a required total sample size of 27 when using an ANOVA: fixed effects, special, main effects, and interactions model. To catch up one possible drop out, which is not expected, a sample size of 28 is included.

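### The sample size of 27 comes from a between-subject ANOVA with 3 df and an unstated effect of about f = 0.80, not from the planned within-patient comparison with 2 df

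*Protocol article*

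**What the plan says.** Section 2.2 (Participants) starts from "A large effect for the investigated three degrees of freedom", continues "with an acceptable alpha error of 0.05 and a 1-beta error of 0.9", and reports that this "results in a required total sample size of 27 when using an ANOVA: fixed effects, special, main effects, and interactions model". One patient is added for dropout, giving 28. The same paragraph gives the effect a second role: "a potential cut off for wearing braces or orthoses was set at a large estimated effect". No number and no metric (f, d, eta squared) is attached to the word large.

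The design is described elsewhere. Sections 2.1 and 2.3 and Table 1 set out a crossover in which each patient completes three runs in one session: rigid orthosis, soft brace and no aid, in one of three orders. Section 4 gives the analysis: "To compare the variances across the means of the three groups we use ANOVA repeated measures". Wilcoxon and Friedman tests are named alongside it.

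**The concern.** The sizing paragraph and the rest of the article describe different experiments.

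- **Model.** A fixed-effects ANOVA compares independent groups. The trial compares conditions within patients, where power depends on the correlation between a patient's repeated measurements. The paragraph gives no correlation.
- **Degrees of freedom.** Three conditions give 3 − 1 = 2. The article names no other contrast with 3 df as the target of the calculation.
- **Effect size.** In the named model, the usual convention for large (f = 0.40) does not come near 27.

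The stated 90% power is therefore not the power of the planned analysis. The effect behind it also serves as the cut-off for whether devices should be worn, and a reader cannot tell which effect that is.

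**Working it through.** **Inputs from section 2.2:** alpha 0.05, power 0.90, numerator df u = 3, N = 27. **Not given, so assumed or solved for:** effect size f, number of groups k, within-patient correlation ρ, sphericity parameter ε.

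**Step 1. Reproduce 27 with the named model.** Power = P(F′ > F crit), where F′ is noncentral F with u and N − k df and noncentrality λ = f²N. I take the smallest N with power of at least 0.90.

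At f = 0.80, u = 3, k = 3:
- N = 27: λ = 0.64 × 27 = 17.28, df 3 and 24, power 0.910.
- N = 26: λ = 0.64 × 26 = 16.64, df 3 and 23, power 0.896.

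So N = 27, the plan's figure. The result is the same for k = 2, 4 or 6, so the unstated number of groups does not matter over that range. With k = 3, exactly 27 requires f between 0.787 and 0.804.

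**Step 2. Try other readings of large in the named model, u = 3.**

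| f | N for 90% power |
|---|---|
| 0.40 (conventional large f) | 93 |
| 0.50 | 61 |
| 0.59 (f² = 0.35) | 45 |
| 0.80 | 27 |
| 1.00 | 19 |

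For f = 0.40 and k = 3: λ = 0.16 × 93 = 14.88 gives power 0.902, and N = 92 gives 0.898.

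**Step 3. Correct only the df.** With u = 2 and k = 3, f = 0.80 needs N = 24 (λ = 15.36, power 0.913; N = 23 gives 0.899), and f = 0.40 needs 83.

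**Step 4. Use the planned type of analysis.** For a within-patient F test with m = 3 conditions, λ = f²Nm/(1 − ρ), with df 2 and 2(N − 1) under sphericity. Without sphericity, λ and both df are multiplied by ε. At f = 0.40 and N = 27:

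| ρ | ε | λ | Power |
|---|---|---|---|
| 0 | 1 | 0.16 × 27 × 3 = 12.96 | 0.889 |
| 0.2 | 1 | 12.96/0.8 = 16.20 | 0.948 |
| 0.5 | 1 | 12.96/0.5 = 25.92 | 0.996 |
| 0 | 0.75 | 12.96 × 0.75 = 9.72 | 0.81 |

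With all 28 patients, ρ = 0 and ε = 1, power is 0.901.

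**Step 5. Solve the same model for the effect detectable with 90% power, N = 27, ε = 1.**

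| ρ | Detectable f |
|---|---|
| 0 | 0.407 |
| 0.5 | 0.288 |
| 0.7 | 0.223 |

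**The case against.** The strongest reply is that the number of patients is probably adequate. The planned comparison is within patients, and for a conventionally large effect 28 patients give about 90% power even with no correlation, and more with positive correlation, if sphericity holds. On that view this is a fault in the write-up and not a threat to the trial. This stands: nothing here calls for more patients. It does not rescue the paragraph. A repeated-measures model with f = 0.40 and ρ = 0 happens to need 28, but that is neither the model nor the df that section 2.2 names.

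A second reply is that 27 has other routes. That is true outside the stated inputs: at 2 df and k = 3, an f of about 0.731 to 0.746 also gives 27. The statement that only f of about 0.80 works is confined to the named model with 3 df.

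A third reply is that the cause of the discrepancy is unknown. That also stands. Because 0.8 is the conventional large value for Cohen's d, a reader might infer that d was entered as f. It is a plausible explanation, but the value was found by working backwards from 27, and the article states no effect value or metric to confirm it.

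Finally, what a non-significant result excludes is read from the confidence interval and not from the planning effect. A corrected paragraph makes the planning claim and the cut-off intelligible, but it does not replace that interval.

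**Conclusion.** The sample-size statement is wrong as written. Two faults need no assumption: a between-subject model is used for a within-patient comparison, and 3 df are used where three conditions give 2. The third is that large is left without a number or metric, and under the named model 27 corresponds to f of about 0.80, whereas f = 0.40 would need 93.

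A reader might infer that the trial is badly underpowered, because the named model at f = 0.40 gives only 33% power with 27 patients. The documents do not support that: the figure applies to independent groups, which this trial does not have. For the within-patient comparison, power at f = 0.40 is about 89% (ρ = 0) to over 99% (ρ = 0.5) under sphericity, and about 81% at ρ = 0 with ε = 0.75.

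These figures rest on assumed values of f, ρ and ε, and on f being defined so that the correlation enters separately. If f is instead defined so that it already absorbs the correlation, with λ = f² × 2(N − 1), then f = 0.40 needs 43 patients (λ = 0.16 × 84 = 13.44). That is why the metric has to be stated.

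**What to change.** Keep 28 patients and replace the paragraph in section 2.2. The new text should:

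- use a repeated-measures calculation with 3 conditions and 2 df, and drop the fixed-effects model and the 3 df;
- give the effect size as a number with its metric and definition;
- state the assumed within-patient correlation and justify it, and state the sphericity assumption;
- give the detectable effect over a range, for example: with 27 evaluable patients, 90% power and sphericity, f of about 0.41 at ρ = 0, 0.29 at ρ = 0.5 and 0.22 at ρ = 0.7;
- express the large-effect cut-off for wearing devices in the same metric;
- not quote 33% as the power of this trial.

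The cost is one rewritten paragraph. Recruitment, design and planned analysis do not change.

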#### 2.2.1. Inclusion Criteria

six months (+/−1 month) after post-traumatic primary unilateral arthroscopically assisted ACLR, with the use of autologous ipsilateral semitendinosus graft;no additional procedures including meniscus sutures during the arthroscopically assisted ACLR;no osteoarthritis surgery during the arthroscopically assisted ACLR other than shaving;no history of injury or disease in the ACL-reconstructed limb prior to the ACL injury within the last 6 months;no history of injury or disease in the adjacent joints, contralateral limb, or spine within the last 6 months;age 18–40 years;Body Mass Index (BMI) smaller or equal to 24.9 kg/m^2^;moderate activity with regard to the rehabilitation plan, physiotherapy, and training therapy;frequent recreational sporting activity prior to the ACL injury.

